### **8.5.2 Use of residual biological samples**

There will be no residual samples from this trial.

## **9 STUDY DISCONTINUATION AND COMPLETION**

### **9.1 Discontinuation and completion**

#### **9.1.1 Study treatment discontinuation and study discontinuation**

The study is made of single dose administration. Therefore, discontinuation of study treatment is not applicable.

However, during the vaccination, the MAP should be removed if any of the following occur:

- Severe (symptomatic bronchospasm with or without urticaria, allergy related edema / angioedema, hypotension) or reaction
- Moderate (Rash, flushing, urticaria, dyspnea, drug fever > 38°C) or worse hypersensitivity reaction
- Severe other adverse event
- Local reaction
- General reaction such as an anaphylactic-like reaction
- General bad tolerance

Participants who do not wish to participate in the study further should NOT be considered withdrawn from the study UNLESS they withdraw their consent (see Section 9.1.2 [Withdrawal of informed consent](#) [WOC]). Where possible, they should return for the assessments indicated in the Assessment Schedule ([Table 5](#)). If they fail to return for these assessments for unknown reasons, every effort (e.g. telephone, e-mail, letter) should be made to contact the participant/pre-designated contact as specified in the lost to follow-up section. This contact should preferably be done according to the study visit schedule.

If the participant cannot or is unwilling to attend any visit(s), the site staff should maintain regular telephone contact with the participant. This telephone contact should preferably be done according to the study visit schedule.

After treatment discontinuation, at a minimum, in abbreviated visits, the following data should be collected at clinic visits or via telephone/email contact:

- New / concomitant treatments
- AEs / SAEs

If discontinuation occurs because treatment code has been broken, please refer to Emergency breaking of treatment code Section 6.6.3 [Emergency breaking of assigned treatment codes](#).

#### 9.1.1.1 Replacement policy

If a participant is not enrolled, a back-up subject will be enrolled until approximately 45 participants have been dosed.

#### 9.1.2 Withdrawal of informed consent

Participants may voluntarily withdraw consent to participate in the study for any reason at any time. WOC occurs only when a participant:

- Does not want to participate in the study anymore,  
and
- Does not want any further visits or assessments  
and
- Does not want any further study related contacts

In this situation, the investigator should make a reasonable effort (e.g. telephone, e-mail, letter) to understand the primary reason for the participant's decision to withdraw his/her consent and record this information.

Where consent to the use of personal and coded data is not required, participant therefore cannot withdraw consent. They still retain the right to object to the further use of personal data.

No further assessments will be conducted, and the data that would have been collected at subsequent visits will be considered missing.

Further attempts to contact the participant are not allowed unless safety findings require communicating or follow-up.

All efforts should be made to complete the assessments prior to study discontinuation. A final evaluation at the time of the participant's study discontinuation should be made as detailed in the assessment schedule (Table 5).

Vaxess or designate will continue to retain and use all research results (data) that have already been collected for the study evaluation.

#### 9.1.3 Lost to follow-up

For participants whose status is unclear because they fail to appear for study visits without stating an intention to discontinue or withdraw, the investigator must show "due diligence" by documenting in the source documents steps taken to contact the participant, e.g. dates of telephone calls, registered letters, etc. A participant should not be considered as lost to follow-up until due diligence has been completed.

#### 9.1.4 Study stopping rules

| Event                                                                          | Number of Participants |
|--------------------------------------------------------------------------------|------------------------|
| Death or any life-threatening SAE                                              | 1                      |
| Any SAE that cannot reasonably be attributed to a cause other than vaccination | 1                      |
| Any withdrawal from the study or withdrawal from study                         | 1                      |

|                                                                                                                                                                                                                                                                                                                                                                                                                                     |   |
|-------------------------------------------------------------------------------------------------------------------------------------------------------------------------------------------------------------------------------------------------------------------------------------------------------------------------------------------------------------------------------------------------------------------------------------|---|
| vaccine(s)/product(s) (by investigator or subject request) following a grade 3 AE that cannot reasonably be attributed to a cause other than vaccination                                                                                                                                                                                                                                                                            |   |
| Any local or general solicited AE leading to hospitalization, or fever > 40°C or 104°F (oral route) that cannot reasonably be attributed to a cause other than vaccination, or necrosis at the injection site, within the 7-day (Days 1-7) post-vaccination period                                                                                                                                                                  | 1 |
| Any grade 3 solicited local AE lasting 48h or more in an investigational group, within the 7-day (Days 1-7) post-vaccination period                                                                                                                                                                                                                                                                                                 | 3 |
| Any grade 3 solicited general AE lasting 48h or more in an investigational group, that cannot reasonably be attributed to a cause other than vaccination, within the 7- day (Days 1-7) post-vaccination period                                                                                                                                                                                                                      | 1 |
| Any grade 3 unsolicited AE in an investigational group, that cannot reasonably be attributed to a cause other than vaccination, within the 7-day (Days 1-7) postvaccination period OR Any grade 3 abnormality in the same pre-specified hematological or biochemical laboratory parameters* in an investigational group, that cannot reasonably be attributed to a cause other than vaccination, within the 7 days post-vaccination | 1 |

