|-----------------------------------|-------------------------------------------------------------------------------------------------------------------------------------------------------------------------------------------------------------------------------------------------------------------------------------------------------------------------------------------------------------------------------------------------------------------------------------------|-------------------------------|
|                                   | Clinic visit on Days 2 (+1), 4 (+1), 8 ( $\pm 2$ ), 15 ( $\pm 2$ ), 29 ( $\pm 2$ ), 57 ( $\pm 2$ ), 85 ( $\pm 7$ ), 119 ( $\pm 7$ ) and 180 ( $\pm 7$ ) will assess adverse events, concomitant medications, and clinical labs.                                                                                                                                                                                                           |                               |
| IMMUNOGENICITY ASSESSMENTS | Serum hemagglutination-inhibition (HAI) titers will be assessed on pre-vaccination on Day 1, and on Days 29 ( $\pm 2$ ), 57 ( $\pm 2$ ), 85 ( $\pm 7$ ), 119 ( $\pm 7$ ) and 180 ( $\pm 7$ ) after vaccination. Anti-HA, virus microneutralization titers, anti-silk fibroin Immunoglobulin G (IgG) and total IgE titers will be assessed on pre-vaccination on Day 1, and on Days 29 ( $\pm 2$ ), and 180 ( $\pm 7$ ) after vaccination. |                               |
| HALTING RULES              | Event                                                                                                                                                                                                                                                                                                                                                                                                                              | Number of Participants |
|                                   | Death or any life-threatening serious AE (SAE)                                                                                                                                                                                                                                                                                                                                                                                            | 1                             |

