### 6.1.3 Treatment Arms/Groups

Participants will be randomized at Day 1 to one of the following “n” treatment arms/groups. The participants will be randomized in a 1:1:1 manner.

Approximately 45 healthy adult participants will be enrolled in the study.

The planned doses are the following:

- Group 1: 15 µg
- Group 2: 7.5 µg
- Group 3: Placebo

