#### **8.4.4 Appropriateness of safety measurements**

The porcine model has been extensively used as a model for studying human skin responses to medical devices. Compared to other common animal models, the epidermis and dermis of the pig has a thickness that is most similar to humans. The pig epidermis ranges from 30 to 140  $\mu\text{m}$ ; human skin ranges from 50 to 120  $\mu\text{m}$ . In addition, the skin of the pig is more firmly attached to the underlying structures as seen in humans ([Abdullahi et al., 2014](#)). Further, pig skin heals through re-epithelialization, unlike mice, rats, and other rodents whose skin heals through contraction. These features make the minipig a particularly useful model for evaluating the local and systemic effects of MIMIX MAPs as well as a useful model for determining if the MIMIX tip material will ultimately be absorbed or ejected and the likely timeline for this event in humans. Vaxess has carried out a pilot evaluation of MAP tolerability and tip persistence and a pilot repeat-dose systemic toxicology study in the Göttingen minipig model. We find that the minipig develops robust immune responses to the VX-103 vaccine antigen. In both pilot studies the results showed transient erythema and edema at the MAP application site that resolved by 28 days post MAP application. The erythema and edema reported, characteristically resolves in the first several days, then reappears and resolves by 28 days. No detectable adverse safety findings were reported. The pilot implantation effects study provides evidence that, by day 90, tip material for MIMIX FLU test articles is absorbed or ejected, there is no longer inflammation, and tissue has been restored to normal structure.

In sum, no adverse systemic events have been reported to date in our preclinical safety studies and local reactogenicity has been limited to transient erythema and edema. These data have been used to inform the design of the Phase 1 clinical trial.

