### 9.1.5 Early study termination by the sponsor

The study can be terminated by Vaxess at any time.

Reasons for early termination

- Unexpected, significant, or unacceptable safety risk to participants enrolled in the study
- Decision based on recommendations from applicable board(s) after review of safety and immunogenicity data
- Discontinuation of study drug development

In taking the decision to terminate, Vaxess will always consider participant welfare and safety. Should early termination be necessary, participants must be seen as soon as possible and treated as a prematurely withdrawn participant. The investigator may be informed of additional procedures to be followed in order to ensure that adequate consideration is given to the protection of the participant's interests. The investigator or sponsor depending on local regulation will be responsible for informing IRBs/IECs of the early termination of the trial.

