### **12.8 Sample size calculation**

The primary objective of this FIH study is to assess the safety, reactogenicity and tolerability of VX-103. A sample size of 30 participants on active treatment (with additional 15 placebo participants) is consistent with historical clinical practice in similar studies.

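### One safety trigger, grade 3 local reactions lasting 48 hours or more, is set at 1 participant in the synopsis and at 3 in Section 9.1.4

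*Protocol*

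**What the plan says.** The synopsis has a table headed "HALTING RULES" with seven events and, for each, a number of participants. The body repeats the seven events under "9.1.4 Study stopping rules".

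The row at issue reads the same in both places: "Any grade 3 solicited local AE lasting 48h or more in an investigational group, within the 7-day (Days 1-7) post-vaccination period". The count beside it is 1 in the synopsis and 3 in Section 9.1.4.

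The other six rows carry a count of 1 in both tables, with only trivial differences in wording. They include the row that covers "necrosis at the injection site, within the 7-day (Days 1-7) post-vaccination period".

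Neither table states what is to be done when a count is reached. No other section defines halting and stopping as different actions or gives one table precedence.

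**The concern.** A pre-set safety trigger has to give one answer for a given set of events. Here, with one or two qualifying participants, the synopsis rule is met and the Section 9.1.4 rule is not. Up to three sites may take part, and staff at different sites could act on different tables in good faith.

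The row matters in this trial. It is a first-in-human study, and Section 4.4 names stopping rules among the measures that limit risk. Local reaction is also the kind of toxicity the sponsor has reason to expect: Section 8.4.4 reports no adverse systemic events in preclinical work and says that "local reactogenicity has been limited to transient erythema and edema". Unlike most of the rows, this one has no condition on causality, so once an event qualifies, the count alone decides whether the rule is met.

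The error can hurt in either direction. If 1 was meant, dosing could continue past the intended trigger. If 3 was meant, a single event could halt the trial without need.

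**Working it through.** **Step 1: compare the tables.**

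| Event (abridged) | Synopsis | Section 9.1.4 |
|---|---|---|
| Death or life-threatening SAE | 1 | 1 |
| SAE not attributable to another cause | 1 | 1 |
| Withdrawal after an attributable grade 3 AE | 1 | 1 |
| Solicited AE with hospitalization, fever above 40°C, or necrosis | 1 | 1 |
| **Grade 3 solicited local AE, 48 h or more** | **1** | **3** |
| Grade 3 solicited general AE, 48 h or more | 1 | 1 |
| Grade 3 unsolicited AE or laboratory abnormality | 1 | 1 |

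With 0 qualifying participants, neither rule is met. With 1 or 2, only the synopsis rule is met. With 3 or more, both are met if the 3 are counted over both active arms. If the 3 must fall within one arm, the conflict can persist beyond 2 events in total.

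**Step 2: inputs for the size.** Section 12.8 gives the number on active treatment: "A sample size of 30 participants on active treatment (with additional 15 placebo participants) is consistent with historical clinical practice". Section 6.1.3 gives the allocation: "The participants will be randomized in a 1:1:1 manner". That makes 15 per active arm and 30 active in all. The protocol gives no rate for this event and no operating characteristics for either count, so there is no figure of its own to reproduce. The true rate p is my assumption, taken as equal in both active arms.

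**Step 3: formulas.** Let X be the number of qualifying participants among the 30 active, binomial with n = 30.

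- Count of 1: P(X ≥ 1) = 1 − (1 − p)^30.
- Count of 3 over both arms: P(X ≥ 3) = 1 − P(X = 0) − P(X = 1) − P(X = 2).
- Count of 3 within one arm: with q = P(3 or more among 15), the chance that either arm reaches 3 is 1 − (1 − q)².
- Conflict: P(X ≥ 1) minus the chance that the count of 3 is met.

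**Step 4: numbers.**

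| | p = 2% | p = 5% | p = 10% |
|---|---|---|---|
| Count of 1 met | 0.4545 | 0.7854 | 0.9576 |
| Count of 3 met, both arms pooled | 0.0217 | 0.1878 | 0.5886 |
| q, one arm of 15 | 0.0030 | 0.0362 | 0.1841 |
| Count of 3 met within either arm | 0.0061 | 0.0711 | 0.3342 |
| **Conflict, pooled** | **0.4328** | **0.5975** | **0.3690** |
| **Conflict, within one arm** | **0.4484** | **0.7143** | **0.6234** |

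As an example, at p = 5% with pooled counting the conflict is 0.7854 − 0.1878 = 0.598 to three places. With counting within an arm it is 0.7854 − 0.0711 = 0.7143.

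Outside this range the pooled conflict shrinks: it is 0.257 at p = 1% (0.2603 − 0.0033) and 0.043 at p = 20% (0.9988 − 0.9558).

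These are chances for the final count once all 30 have been dosed. They are not chances of halting in time to spare someone a dose, which depends on an enrolment pace the protocol does not give.

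**The case against.** The strongest reply is that the two headings describe two tiers, a pause at 1 and a stop at 3. Six rows that agree at 1 do not exclude this, because a pause and a stop could both be set at 1 for graver events. But the protocol nowhere says so. If that was the intention, the definition is missing, and it still has to be written.

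A second point is that neither table states an action, so strictly the conflict is between a rule that is met and a rule that is not. That is correct. The headings nevertheless make the intended consequence plain enough for the difference to matter.

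Third, the rates are not anchored in the protocol, and preclinical erythema described as transient does not show that grade 3 events are likely. Appendix 1 requires erythema wider than 10 cm for grade 3, around a 1 cm square patch. This stands, and the percentages are illustrations only. However, the assessment schedule also lists the Appendix 2 items as solicited local AEs, and some of their grade 3 bars are lower: bruising wider than 5 cm, or a pigmented area of 1 cm or more that is very clearly defined. A qualifying event is therefore not remote.

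Fourth, the harm is bounded. Each participant has a single dose, so a halt protects only those not yet dosed. Death, life-threatening or attributable SAEs, hospitalization for a solicited AE, site necrosis and withdrawal after an attributable grade 3 AE all trigger at 1 in both tables. Section 9.1.5 adds "The study can be terminated by Vaxess at any time". All of this limits the consequence. Sponsor discretion does not replace a pre-set rule.

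**Conclusion.** The concern holds. The current text gives one identically worded safety trigger two counts, 1 and 3, and offers no way to choose between them. This follows from reading the two rows and rests on no assumption.

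The size does rest on assumptions: a common true rate in both active arms, independent participants, and all 30 dosed. At rates of 2% to 10%, the chance of ending with one rule met and the other not lies between 37% and 71%, depending on the rate and the counting unit. At 1% with pooled counting it is 26%.

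The gap is confined to grade 3 local reactions lasting 48 hours or more. It should be closed before anyone is dosed, because a first-in-human safety trigger needs a single value. The protocol does not show which value was intended.

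**What to change.** Before dosing, the sponsor should choose one count for this row and enter it in both the synopsis and Section 9.1.4. Until that is done, the stricter count of 1 should apply; this is a cautious interim choice, not a reading of what was meant.

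If a pause at 1 and a stop at 3 were intended, both tables should state the two tiers and the action at each.

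If 3 is kept, one sentence should say whether it is counted within a single active arm or over both. At an assumed 10% rate that choice moves the chance of meeting the trigger from 33% to 59%. At a count of 1 it makes no difference.

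The cost is one protocol amendment that corrects one row in two tables, plus a sentence or two if tiers or a count of 3 are retained. No added data or participants are needed.

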|                                   | Any grade 3 unsolicited AE in an investigational group, that cannot reasonably be attributed to a cause other than vaccination, within the 7-day (Days 1-7) postvaccination period OR Any grade 3 abnormality in the same pre-specified hematological or biochemical laboratory parameters in an investigational group, that cannot reasonably be attributed to a cause other than vaccination, within the 7 days post-vaccination        | 1                             |
| FOLLOW-UP DURATION         | Participants will be followed for up to 180 days ( $\pm 7$ ) after vaccination.                                                                                                                                                                                                                                                                                                                                                           |                               |
| ENDPOINT PARAMETERS        | a) Safety analysis will be identified within the Statistical Analysis Plan and includes:                                                                                                                                                                                                                                                                                                                                                  |                               |

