All adverse events must be treated appropriately. Treatment may include one or more of the following:

- Dose not changed
- Dose Reduced/increased
- Drug interrupted/withdrawn

6. Its outcome

Conditions that were already present at the time of informed consent should be recorded in medical history of the participant.

AEs (including lab abnormalities that constitute AEs) should be described using a diagnosis whenever possible, rather than individual underlying signs and symptoms.

Once an AE is detected, it must be followed until its resolution or until it is judged to be permanent (e.g. continuing at the end of the study), and assessment must be made at each visit (or more frequently, if necessary) of any changes in severity, the suspected relationship to the interventions required to treat it, and the outcome.

Information about known adverse reactions for the investigational drug can be found in the IB.

Abnormal laboratory values or test results constitute adverse events only if they fulfill at least one of the following criteria:

- they induce clinical signs or symptoms
- they are considered clinically significant
- they require therapy

Clinically significant abnormal laboratory values or test results must be identified through a review of values outside of normal ranges/clinically notable ranges, significant changes from baseline or the previous visit, or values which are considered to be non-typical in participant with the underlying condition or disease.

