## 10.2 Additional Safety Monitoring

| SERUM                                                | Mild: Grade 1 | Moderate: Grade 2 | Severe: Grade 3 | Potentially Life Threatening: Grade 4 |
|------------------------------------------------------|---------------|-------------------|-----------------|---------------------------------------|
| ALT, AST (liver function tests) increase by a factor | 1.1-2.5 x ULN | 2.6-5.0 x ULN     | 5.1-10 x ULN    | >10 x ULN                             |
| Cr mg/dL                                             | 1.5-1.7       | 1.8-2.0           | 2.1-2.5         | >2.5                                  |
| Blood Urea Nitrogen- BUN mg/dL                       | 23-26         | 27-31             | >31             | Dialysis                              |

- The laboratory values serve as a guide and are dependent on the institutional reference ranges.

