| Calcium – hypercalcemia mg/dL                                                          | 10.5 – 11.0      | 11.1 – 11.5      | 11.6 – 12.0       | > 12.0                                    |
| Magnesium – hypomagnesemia mg/dL                                                       | 1.3 – 1.5        | 1.1 – 1.2        | 0.9 – 1.0         | < 0.9                                     |
| Phosphorous – hypophosphatemia mg/dL                                                   | 2.3 – 2.5        | 2.0 – 2.2        | 1.6 – 1.9         | < 1.6                                     |
| CPK – mg/dL                                                                            | 1.25 – 1.5 x ULN | 1.6 – 3.0 x ULN  | 3.1 –10 x ULN     | > 10 x ULN                                |
| Albumin – Hypoalbuminemia g/dL                                                         | 2.8 – 3.1        | 2.5 – 2.7        | < 2.5             | --                                        |
| Total Protein – Hypoproteinemia g/dL                                                   | 5.5 – 6.0        | 5.0 – 5.4        | < 5.0             | --                                        |
| Alkaline phosphate – increase by factor                                                | 1.1 – 2.0 x ULN  | 2.1 – 3.0 x ULN  | 3.1 – 10 x ULN    | > 10 x ULN                                |
| Liver Function Tests –ALT, AST increase by factor                                      | 1.1 – 2.5 x ULN  | 2.6 – 5.0 x ULN  | 5.1 – 10 x ULN    | > 10 x ULN                                |
| Bilirubin – when accompanied by any increase in Liver Function Test increase by factor | 1.1 – 1.25 x ULN | 1.26 – 1.5 x ULN | 1.51 – 1.75 x ULN | > 1.75 x ULN                              |
| Bilirubin – when Liver Function Test is normal; increase by factor                     | 1.1 – 1.5 x ULN  | 1.6 – 2.0 x ULN  | 2.0 – 3.0 x ULN   | > 3.0 x ULN                               |
| Cholesterol                                                                            | 201 – 210        | 211 – 225        | > 226             | ---                                       |
| Pancreatic enzymes – amylase, lipase                                                   | 1.1 – 1.5 x ULN  | 1.6 – 2.0 x ULN  | 2.1 – 5.0 x ULN   | > 5.0 x ULN                               |

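### The laboratory halting clause names only grade 3, so read literally a worse, grade 4 value does not meet it (minor; nearly free to fix)

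*Protocol*

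**What the plan says.** The last row of the table in Section 9.1.4 has two halves, each with a threshold of one participant. The first half concerns clinical events: "Any grade 3 unsolicited AE in an investigational group". The second half is the laboratory clause: "Any grade 3 abnormality in the same pre-specified hematological or biochemical laboratory parameters". It applies to an investigational group, carries a causality condition, and is limited to 7 days after vaccination. The halting rules in the synopsis repeat it: "Any grade 3 abnormality in the same pre-specified hematological or biochemical laboratory parameters in an investigational group".

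Section 10.2 grades three serum rows. In the row "ALT, AST (liver function tests) increase by a factor", grade 3 is 5.1–10 x ULN. The next column is headed "Potentially Life Threatening: Grade 4" and begins above 10 x ULN. Appendix 3 has the same bands in its serum table ("ALT, AST increase by factor"). Section 10.2 qualifies the limits: "The laboratory values serve as a guide and are dependent on the institutional reference ranges".

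Section 10.1.1 governs when a laboratory result becomes an adverse event: "Abnormal laboratory values or test results constitute adverse events only if they fulfill at least one of the following criteria". The criteria are clinical signs or symptoms, clinical significance, or a need for therapy. Severity in that section has three levels and is defined by effect on normal activities.

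**The concern.** On these scales grade 4 is a band of its own and is not included in grade 3. A clause that names grade 3 and stops there has an upper edge. For a parameter with a closed grade 3 band, the rule is met by the less abnormal result and not met by the more abnormal one, which is the wrong way round for a safety threshold.

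At stake is consistent use of the formal stopping rule in a first-in-human study at up to three sites. One site may read 'or higher' into the clause while another applies it as printed and sends a grade 4 value through the adverse event and seriousness assessments first.

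**Working it through.** No sample size, power or error rate is involved. The check sets the clause against the grading bands and then counts the rows that could be affected.

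**1. The clause applied to ALT/AST.** Assume that ALT/AST is on the pre-specified list, that the value cannot reasonably be attributed to another cause, and that it falls within 7 days.

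| ALT/AST | Grade (Section 10.2, Appendix 3) | Clause as printed | With 'grade 3 or higher' |
|---|---|---|---|
| 6 x ULN | 3 | met | met |
| 10 x ULN | 3 | met | met |
| 10.1 x ULN | 4 | not met | met |
| 15 x ULN | 4 | not met | met |

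As printed, the trigger is the interval 5.1–10 x ULN. With the added words it is every value from 5.1 x ULN upward.

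**2. Whether the clause will be used.** Section 3 schedules hematology and chemistry on Day 4, inside the 7-day window.

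**3. Other routes to a halt for a grade 4 value.**
- The unsolicited-event half of the same row. The value must first qualify as an adverse event under Section 10.1.1 and then be rated severe, which means that it prevents normal activities. A laboratory rise without symptoms need not do so.
- The two SAE rows. The value must be judged serious. Under Section 10.1.2, life-threatening means at risk of death at the time, so the grade 4 column heading does not make a value serious by itself. Medically significant is also a judgement.

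Each route adds a judgement to the causality judgement that a grade 3 value already needs.

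**4. How many parameters.** The clause refers to a pre-specified list that the text supplied does not show, so only a range can be given.
- If the list is the Section 10.2 table: 3 rows (ALT/AST, creatinine, BUN), less BUN, whose grade 3 is open-ended (above 31 mg/dL). 3 − 1 = **2**. Creatinine grade 3 is 2.1–2.5 mg/dL and grade 4 is above 2.5 mg/dL.
- If the list is everything graded in the Appendix 3 blood tables: rows with a grade 4 entry are 13 (hematology and coagulation) + 18 (serum) = 31. Remove 3 with an open-ended grade 3 (eosinophils, BUN, high glucose) and fibrinogen decrease, which is not in Table 7: 31 − 3 − 1 = **27**. If PT and PTT are not drawn in the window, 27 − 2 = **25**.

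PT and PTT are uncertain. Section 3 names only hematology and chemistry on Day 4, but the synopsis speaks generally of clinical labs at the early visits, and the laboratory rows of Table 5 cannot be read in the copy supplied.

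**The case against.** The strongest answer is that nobody will be misled. The evident meaning is 'grade 3 or higher', and no section exempts grade 4. Section 8.4.1 requires every abnormal laboratory result to be evaluated against the adverse event criteria, and clinical significance alone is enough. A vaccine-attributable ALT/AST above 10 x ULN would plausibly be judged medically significant under Section 10.1.2. It would then halt the study at one participant through the row for related SAEs. Section 9.1.5 also lets the sponsor stop at any time. Nor is the grade 3 clause automatic: it needs a causality judgement, and its limits are only a guide.

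Most of this stands, and it makes the practical gap small. What it does not do is repair the clause, because each of those routes needs a further judgement that a grade 3 value does not.

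A reader might go further and infer that other rows of the table have the same fault. The documents do not support that:
- **Withdrawal and unsolicited-event rows.** The scale in Section 10.1.1 ends at severe, so there is no worse grade to miss and 'or higher' would refer to nothing. Using a grade number for a three-level scale is only a matter of terminology.
- **Solicited events.** The fourth row already halts on hospitalization, fever above 40°C and necrosis. It does not name an emergency room visit without admission, or exfoliative dermatitis. But Section 10.1.2 gives intensive emergency room treatment as an example of a medically significant event, and exfoliative dermatitis could also qualify. A one-participant halt for any grade 4 solicited event would stop the study for an emergency room visit over a local symptom, with no duration or causality test. That is a design preference and does not correct an error.

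**Conclusion.** The laboratory halting clause is wrong as written in Section 9.1.4 and in the synopsis: taken literally, grade 3 meets it and grade 4 does not. The matter is minor, because the intent is very likely 'or higher' and a grade 4 value has other, judgement-dependent routes to a halt. It would be too much to say that the protocol exempts grade 4 values or that such a value would go without a halt.

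The conclusion is conditional on a parameter on the pre-specified list, a value that meets the causality condition, and the 7-day window. ALT/AST as the example is an assumption. The number of affected parameters is not determinable from the text supplied: 2 of 3 rows under the Section 10.2 list, and about 25 to 27 rows at most under Appendix 3.

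**What to change.** In the laboratory clause of both the Section 9.1.4 table and the synopsis table, replace 'grade 3' with 'grade 3 or higher'. Leave the withdrawal row, the unsolicited-event half of the last row and the solicited-event rows as they are on this point.

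The cost is a two-word change in two places and a slightly higher chance of a halt. The existing causality condition still screens out values with another explanation. Sites that already read the clause as including grade 4 will see no difference.
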